## Methods/design

### Design and setting

A double-blind RCT with two parallel groups will be conducted. This RCT will conform to the Standard Protocol Items: Recommendations for Interventional Trials (SPIRIT) 2013 Statement (Additional file 1). The proposed clinical trial will be implemented in the IBD Clinic at Imam Khomeini Hospital, affiliated to Ahvaz Jundishapur University of Medical Science, Iran, for 12 weeks to assess the efficacy of daily adjunctive supplementation with 3 g ginger in patients with active UC. An overview of the study is illustrated in Fig. 1.

**Fig. 1 Fig1:**
[figure not shown]
Overview of RCT protocol

### Participants

The participants will be 44 patients with active UC. The inclusion criteria for eligibility of the participants will be as follows: moderate to severe active UC (according to the partial Mayo score; PMS); absence of fulminant UC signs; age range between 18 and 50 years; BMI between 18.5 and 30 kg/m^2^; absence of cancer or hepatic, renal, thyroid, and other gastrointestinal disorders; no sensitivity to ginger; no intake of nutritional supplements in the previous 8 weeks; and no involvement in other trials in the previous 12 weeks.

The exclusion criteria will be the following: use of anti-TNF-α drugs such as infliximab; pregnancy during the study; postmenopausal women; use of nonsteroidal anti-inflammatory and anti-diarrheal drugs; and use of anticoagulant, antidiabetic, or anti-pressure medications.

### Ethical considerations and trial registration

The Medical Ethics Committee of Ahvaz Jundishapur University of Medical Sciences approved this proposal, and it is in accordance with the Declaration of Helsinki (approval no.: IR.AJUMS.-REC.1397.893). Each participant will sign an informed written consent form before enrollment to this RCT. All collected data will be held confidential. The registration number for the Iranian Registry of Clinical Trials (IRCT registration no.) is IRCT20190129042552N1.

### Sample size

The sample size was calculated according to primary outcomes (if data were available), and the maximum calculated sample size was considered. The sample size was based on the changes observed in the TNF-α in the study by Mozafari Khosravi [13] as a result of ginger supplementation. Considering a type I error of 0.05, a test power of 90%, and follow-up loss of 10%, the sample size required in each group was calculated to be 22 patients. To achieve the estimated sample size, all patients will be included in the study in case they meet the inclusion criteria and are willing to participate in the study.

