Ginger, viz. *Zingiber officinale* from the Zingiberacea family, is a rhizome widely used as a spice [12], which contains many active phenolic components such as gingerol, shogaol, and zingeron.

These components show antioxidative, anti-inflammatory, and immunomodulatory properties. A clinical trial evaluated the effect of ginger supplementation in older patients with osteoarthritis. This trial show a reduction in inflammatory markers like TNF-α and IL-1β [13]. In addition, another trial reported a reduction in nitric oxide and hs-CRP levels in ginger-supplemented osteoarthritis patients compared to the control group [14]. A randomized clinical trial conducted by Aryaeian et al. showed that ginger supplementation could improve the disease activity score and modulate some inflammatory genes in rheumatoid arthritis patients [15].

Data also have revealed that ginger suppresses nuclear factor kappa B (NF_κ_B) and ameliorates UC in experimental models [16, 17]. In a study by Allah et al., ginger administration (400 mg/kg) significantly improved the effects of acetic acid-induced colitis by decreasing the weight-to-length ratio of the colon and macroscopic and microscopic manifestation of colon specimens. These effects were associated with a significant decrease in NFkB expression and a decrease in TNF-α, IL-10, and the total peroxide levels in the colon. In this study, the therapeutic effects of ginger were shown to be more than preventive effects [16]. Dileep et al. investigated the anti-inflammatory effects of an alcohol extract of ginger (700 mg/kg/day) in ulcerative colitis induced by acetic acid in rats. The results showed that increased levels of carbonyl protein, TNF-α, IL-1β, and prostaglandin E2 decreased significantly in the colon. Significant increases in the levels of superoxide dismutase, catalase, reduced glutathione, glutathione peroxidase, and IL-10 were also observed in this study. Histological examination revealed a decrease in bleeding and edema in the colon of the treated group [18].

To the best of the authors’ knowledge, no published data exist on the effect of ginger supplementation on patients with UC; therefore, a randomized controlled trial (RCT) will be designed to determine the effect of ginger supplementation on the clinical status, serum levels of some inflammatory markers (i.e., TNF-α and hs-CRP), total antioxidant capacity (TAC), and expression of miR-21 in patients with active UC.

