### Hypothesis and aim

The research hypothesis addressed is that ginger supplementation along with taking standard medications improves clinical and biochemical parameters. The primary objectives of this RCT is to assay the effect of 12-week ginger supplementation on inflammatory markers (TNF-α and hs-CRP) and TAC in patients with active UC. The secondary objective will be also to determine clinical score and miR-21 expression. For all outcomes, including the primary and secondary outcomes, measurements will be made at the beginning and the end of the intervention, and changes from baseline within groups and final values between groups will be evaluated.

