### Randomization and blinding

The patients will be randomly allocated to one of the intervention group (Group A) (standard treatment + ginger capsules, *n* = 22) or control group (Group B) (standard treatment + placebo capsules, *n* = 22). Random allocation sequence will be generated using a random number table by a third party who will be operationally independent from the study investigators and will generate a simple design. Ginger and placebo bottles will be also encoded based on random numbers by someone other than researchers, and odd or even numbers will be allocated randomly to Group A or Group B. To decrease the probability of bias, clinicians and those analyzing the results will be blind to the allocated groups. To maintain blinding, ginger and placebo bottles will be similar in appearance. Randomization codes of the study will remain confidential until all the patients have completed the study protocol.

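### The 90% power was derived from changes in TNF-α at one 5% level and is not established for the planned comparison of final values or for the three primary outcomes jointly

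*Protocol article*

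**What the plan says.** The Sample size section of the protocol article gives the basis of the calculation: "The sample size was based on the changes observed in the TNF-α" in an earlier ginger trial, which the Background describes as one in older patients with osteoarthritis. The error rates and loss follow: "Considering a type I error of 0.05, a test power of 90%, and follow-up loss of 10" per cent. The result is that "the sample size required in each group was calculated to be 22 patients". The same section says that the primary outcomes were considered where data existed and that the largest resulting size was taken. It does not say which outcomes had data.

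The Abstract and the Hypothesis and aim section name three primary outcomes: TNF-α, hs-CRP and total antioxidant capacity (TAC). For all outcomes, Hypothesis and aim says that "changes from baseline within groups and final values between groups will be evaluated".

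The Analysis section agrees. Values at the start and at the end are compared between groups by t-test or Mann-Whitney test. Two further between-group analyses are planned:

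- a comparison of percentage change from baseline;
- a general linear model adjusted for confounders, with type of medication as the example. The baseline value of the outcome is not named as a covariate.

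Each test is judged at p < 0.05. No between-group analysis is named as the main one.

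**The concern.** Power belongs to a particular comparison: an effect, an SD, a test and a significance level. Here the sizing input is a change in one marker, while the stated between-group comparison is of final values, and absolute change is compared only within groups. The SD of a change and the SD of a final value are generally different, so the same mean effect can have quite different power on the two scales. In addition, one 90% figure at one 5% level stands in front of three primary outcomes.

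At stake is how a null result will be read. A reader would set it against 90% power, although the document does not show that the comparison made, or the set of three outcomes, had that power.

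**Working it through.** **Inputs from the documents.** Alpha 0.05 (sidedness not stated), power 90%, loss 10%, 22 per group, 1:1 allocation (Sample size; Randomization and blinding). Three primary outcomes (Abstract; Hypothesis and aim).

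**Assumptions, because the documents give no figure.** Two-sided test; sizing based on the SD of change; equal SDs at baseline and end; r, the baseline-to-end correlation, varied over a range.

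**1. The plan's own figure.** The assumed difference and SD are not given, so 22 per group can be back-solved but not reproduced. Allowing for 10% loss, 19/0.9 = 21.1 rounds up to 22, and 20 × 1.1 = 22. So 22 fits 19 or 20 evaluable per group (22 × 0.9 = 19.8). By the normal approximation the implied standardised effect is d = (1.960 + 1.282) × √(2/n), which is 1.05 at n = 19 and 1.03 at n = 20. By the noncentral t, 90% power needs d = 1.081 at n = 19 and 1.052 at n = 20. The arithmetic is therefore coherent for an effect of about 1.05. The steps below use n = 20, d = 1.052 and the noncentral t.

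**2. Conversion to final values.** With equal SDs at both visits, SD(change) = SD(final) × √(2(1 − r)). The same mean difference in final-value SD units is then d(final) = 1.052 × √(2(1 − r)).

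**3. Adding the baseline as a covariate.** The residual SD is SD(final) × √(1 − r²), so d(adjusted) = d(final)/√(1 − r²).

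| r | d(final) | Power, final values unadjusted | d(adjusted) | Power, baseline-adjusted |
|---|---|---|---|---|
| 0.3 | 1.245 | 97% | 1.305 | 98% |
| 0.5 | 1.052 | 90% | 1.215 | 96% |
| 0.6 | 0.941 | 83% | 1.176 | 95% |
| 0.7 | 0.815 | 71% | 1.141 | 94% |
| 0.8 | 0.665 | 54% | 1.109 | 93% |
| 0.9 | 0.470 | 31% | 1.079 | 91% |

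The two scales agree at r = 0.5. The unadjusted final-value test has more than 90% power below that and less above it.

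**4. Three primary outcomes.** What 90% means jointly depends on a success rule that the article does not state. These are alternatives and do not add up:

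- Each outcome judged separately at 0.05: the power for TNF-α is unchanged. With independent tests, the chance of at least one false positive is 1 − 0.95³ = 14.3%.
- Alpha split as 0.05/3: the power for an effect of 1.052 on the change scale is 79%.
- All three must succeed, with 90% each and independence: 0.9³ = 73%.

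**The case against.** The strongest reply is that nothing here proves the 90% wrong. The difference, SD and r are not given, and for r of 0.5 or less the final-value test has at least the stated power. The word for changes in the Sample size section may simply mean the effect that was observed, in which case the SD used could already be that of final values. A reader might infer from the lower rows of the table that the trial is underpowered. The documents do not support that, since nothing in them favours r above 0.5. This part of the reply stands and limits the conclusion to what has not been established.

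A reader might also infer that having three primary outcomes lowers the power. It does so only if alpha is split or all three must succeed, and the article states neither rule. The Sample size section also says that the maximum over the primary outcomes with data was taken, so hs-CRP or TAC may have been covered individually. That stands too, but it sets no joint rule and leaves open which outcomes were covered.

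Final values are not the only planned between-group comparison. However, percentage change is not absolute change, and the general linear model is not said to include baseline, so neither is shown to be the quantity behind the 90%.

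Finally, the unstated effect size and the borrowing from osteoarthritis are not errors. A condensed article may leave the inputs to the full protocol, and the Background says that no data on ginger in UC patients have been published.

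**Conclusion.** The point holds as a mismatch between two statements in the article: the trial is sized on changes in TNF-α and compares final values between groups. The 90% is not established for that comparison or for the three primary outcomes jointly. No arithmetic error is shown, because 22 per group is compatible with a standardised effect of about 1.05 and 10% loss.

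Under the assumptions listed, power for the unadjusted final-value test on TNF-α runs from 97% at r = 0.3 to 54% at r = 0.8. Where this trial falls in that range cannot be told from the document. The point merits a change because the remedy removes the dependence on r almost entirely and needs no more patients.

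**What to change.** Keep 44 patients and all three primary outcomes.

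1. Name one main between-group analysis for each primary outcome: the general linear model already planned, on the end value, with that outcome's baseline value as a covariate. Under the assumptions above it has about 91% to 98% power for r from 0.3 to 0.9. The unadjusted comparison of final values and the percentage change become supporting analyses.
2. Restate the power: with about 20 evaluable patients per group, the 90% applies to TNF-α alone, at an unadjusted two-sided 0.05, for a standardised effect of about 1.05 on the change scale. Say that it does not apply to the three primary outcomes jointly.

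The cost is a slightly less favourable power statement. No patients, visits or assays are added, since baseline values are already to be measured. Naming a main analysis is a change to the plan and not only to its wording. As the Trial status section reports recruitment under way, it should be recorded as a dated amendment before the randomisation codes are opened.

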### Randomization and blinding

The patients will be randomly allocated to one of the intervention group (Group A) (standard treatment + ginger capsules, *n* = 22) or control group (Group B) (standard treatment + placebo capsules, *n* = 22). Random allocation sequence will be generated using a random number table by a third party who will be operationally independent from the study investigators and will generate a simple design. Ginger and placebo bottles will be also encoded based on random numbers by someone other than researchers, and odd or even numbers will be allocated randomly to Group A or Group B. To decrease the probability of bias, clinicians and those analyzing the results will be blind to the allocated groups. To maintain blinding, ginger and placebo bottles will be similar in appearance. Randomization codes of the study will remain confidential until all the patients have completed the study protocol.

### Intervention

During the 12-week intervention, both groups will continue the use of the prescribed medications. Patients in the intervention group will receive three ginger capsules on a daily basis (i.e., one capsule after each main meal), and each capsule will also contain 1 g of dried ginger rhizome. Notably, a human equivalent dose had been calculated in an animal study [14] using a conversion factor [19]. Patients in the control group will receive three placebo capsules daily; each capsule will contain 1 g of starch as a placebo, which looks like a ginger capsule in appearance. Ginger and placebo capsules are being made by the Green Plants Life Company. The method and the time of taking the capsules are labeled on the bottles. Patients in both groups will be requested not to change their typical diet and physical activities and also avoid the use of nutritional or ginger supplements, ginger candy, and ginger seasoning, as well as ginger tea and other herbal remedies during the study.

Ginger and placebo capsules will be delivered in identical containers for 4 weeks. The patients will be asked to give back the containers at the end of each fourth week for use in calculating their compliance rate. To ensure the ordered use of capsules as well as accurate implementation of the RCT, researchers will contact the patients via phone calls or short message service (SMS) each week.

### Measurements

At the onset of this RCT, demographic characteristics information will be collected via interviews and records, and relevant questionnaires will be completed. Weight will be also measured, while participants are wearing light clothes and no shoes, to 0.1-kg accuracy on a Seca scale, height will be measured, without shoes, using a 0.5-cm accuracy on a Seca stadiometer, and BMI will be calculated by dividing the weight (kg) by the height squared (m^2^).

In addition, the clinical status of the patients will be characterized by PMS and the Simple Clinical Colitis Activity Index (SCCAI) at pre- and post-intervention stages. Notably, the PMS is made up of three noninvasive parts of the complete Mayo score, which includes frequency of defecation, rectal bleeding, and a physician’s assessment of disease severity. Each of the parameters has a score from 0 to 3, and the maximum total score is 9. This score divides patients into those with inactive UC (i.e., in remission) and into those with active UC (i.e., mild, moderate, and severe). The clinical response is also defined as at least a 2-point reduction in the Mayo clinical score. The SCCAI includes the frequency of defecation during the night and day, defecation urgency, blood in stool, general sense of well-being, and external manifestations of the disease. The total score can range from 0 to 19.

Biochemical parameters consist of serum levels of TNF-α (ng/l), hs-CRP (mg/l), and TAC (u/ml) which will be evaluated by the enzyme-linked immunosorbent assay (ELISA) kits and miR-21 expression, which will be measured through reverse-transcription polymerase chain reaction (RT-PCR). At the beginning and the end of the study, a 5-ml venous blood sample (in a regular tube) will be collected in ethylenediaminetetraacetic acid (EDTA) tubes after approximately 12 h over-night fasting, and it will be centrifuged at 1500 g for 15 min and stored in −70 °C frigid temperature.

Physical activity will be evaluated by the short form of International Physical Activity Questionnaire (IPAQ) and calculated as MET-min/week. For dietary evaluation, 3 days of 24-h food recall (1 day of weekend and 2 days of the week) will be completed and then analyzed by Nutritionist IV software to determine the energy, protein, carbohydrate, and fat intake. Physical activity and dietary evaluation will be conducted at the onset and the end of the study.

### Analysis

The data will be analyzed using the Statistical Package for the Social Sciences (IBM SPSS Statistics 22. Ink). Normality of all quantitative variables (age, serum level of TNF-α, hs-CRP, TAC, and expression of mir-21) will be also evaluated by the Kolmogorov-Smirnov test. For normal distribution variables, independent sample t-test and paired sample t-test will be also used to compare parameters at the beginning and the end of the study between and within groups, respectively. The Mann-Whitney U test and Wilcoxon signed-rank test as nonparametric alternatives will be further applied to compare sample parameters between and within groups, respectively. In adjusted models for confounding variables (such as the type of medication), a general linear model (GLM) (univariate type) will be used for each certain parameter to compare mean values between groups. For each certain variable (primary and secondary outcomes), the percentage change will be also calculated (i.e., by subtracting the beginning from the final value, dividing by the beginning value, and multiplying by 100) and will be compared between groups by independent sample t-test or Mann-Whitney U, as well as by GLM univariate tests. The results will be presented as the mean ± SD, and differences will be considered statistically significant at *p* < 0.05. Intention-to-treat analysis will be employed if possible.

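### The test for each primary marker is chosen by a normality pre-test on the trial's own data while means are reported regardless, so p-value and reported effect can describe different quantities

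*Protocol article*

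**What the plan says.** All of this stands in the Analysis section of the protocol article.

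- Normality of age, TNF-α, hs-CRP, TAC and miR-21 expression "will be also evaluated by the Kolmogorov-Smirnov test". The section does not say whether arms are tested separately or pooled, at which time point, or with critical values corrected for an estimated mean and SD.
- Variables judged normal go to independent and paired t-tests. Mann-Whitney and Wilcoxon tests "as nonparametric alternatives will be further applied to compare sample parameters between and within groups, respectively".
- Percentage change from baseline has the same either/or choice.
- The adjusted analysis is a univariate general linear model that compares mean values between groups. The only adjustment variable named, as an example, is type of medication.
- "The results will be presented as the mean ± SD", with no exception for variables tested by ranks.

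TNF-α, hs-CRP and TAC are the primary outcomes (Abstract; Hypothesis and aim), so the rule governs the main comparisons of the trial.

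**The concern.** A t-test asks whether two means differ. A Mann-Whitney test asks whether values in one arm tend to exceed those in the other. Under the stated rule, a diagnostic on the outcome data settles which question is asked of each primary marker. A marker judged non-normal would get a rank test unadjusted and a comparison of means adjusted, with mean ± SD printed beside a p-value that does not test those means.

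The diagnostic is also weak at this sample size. Two trials from the same population could take different routes, and so could two time points of the same marker. At stake are a clear statement of what the primary result estimates and, if the markers are skewed, some of the power of a 44-patient trial planned with "a test power of 90"%.

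**Working it through.** **1. Evaluable size.** The Sample size section states "follow-up loss of 10"% and that "the sample size required in each group was calculated to be 22 patients". 22 × 0.9 = 19.8, so about 20 per arm. The figure of 22 cannot be reproduced, because no mean difference or SD is given. Solving backwards, 19 / 0.9 = 21.1, rounded up to 22, implies a standardised difference of (1.960 + 1.282) × √(2/19) = 1.05 (two-sided). Nothing below depends on that value.

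**2. Assumed distributions.** The document gives none. Take lognormal data with log-SD s, for which skewness = (e^(s²) + 2) × √(e^(s²) − 1).
- s = 0.5: (1.284 + 2) × √0.284 = 1.8
- s = 1.0: (2.718 + 2) × √1.718 = 6.2

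**3. How often the pre-test misses the skewness** (5% level, 40,000 simulated samples per setting). Corrected critical values are 0.192 (n = 20) and 0.139 (n = 40); uncorrected values are 0.304 and 0.215.

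| Distribution | Skewness | n = 20 corrected | n = 20 uncorrected | n = 40 corrected | n = 40 uncorrected |
|---|---|---|---|---|---|
| Lognormal, s = 0.5 | 1.8 | 66% | 99% | 39% | 94% |
| Lognormal, s = 0.8 | 3.7 | 35% | 93% | 8% | 65% |
| Lognormal, s = 1.0 | 6.2 | 21% | 84% | 2% | 39% |
| Gamma | 1.0 | 82% | 100% | 67% | 99% |
| Gamma | 2.0 | 42% | 97% | 10% | 80% |

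**4. Which test is then used.** Suppose Mann-Whitney is used if the corrected test rejects in either arm.
- s = 0.5: 1 − 0.66² = 0.56. Simulation gives 57% Mann-Whitney and 43% t-test for one and the same population.
- s = 1.0: 1 − 0.21² = 0.96, so the route is nearly always Mann-Whitney.

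With arms pooled and s = 0.5, the pre-tests at baseline and at the end disagree in about 45% of trials. With a true effect of 0.8 log-SD, the t-test and Mann-Whitney disagree on significance in 12% (s = 0.5) to 22% (s = 1.0) of trials.

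**5. Type I error of the two-step rule.** 0.046 to 0.056 across the settings and runs.

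**6. Power, like for like.** 20 per arm, effect 0.8 log-SD, baseline-to-final correlation r = 0.5 on the log scale. The second run had 5,000 trials.

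| Analysis | Run 1, s = 0.5 / 1.0 | Run 2, s = 0.5 / 1.0 |
|---|---|---|
| Pre-test per arm (corrected), final values | 67% / 68% | 68.1% / 67.2% |
| Log-scale t-test, final values | 68% / 70% | 69.6% / 69.4% |
| Raw-scale ANCOVA with baseline | 74% / 58% | 74.6% / 58.1% |
| Log-scale ANCOVA with baseline | 79% / 81% | 81.2% / 80.7% |

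The log-scale rows cannot truly depend on s, so their differences of about 2 points are simulation error. The exact power of the log-scale t-test is 69.3%. For log-scale ANCOVA the effect becomes 0.8 / √(1 − 0.5²) = 0.924. The noncentrality is then 0.924 × √(20/2) = 2.92, which on 37 degrees of freedom gives about 81%.

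Taken apart, the gains are:
- **Dropping the pre-test and fixing the log scale, without baseline:** 68 − 67 = 1 and 70 − 68 = 2 points in run 1; 1.5 and 2.2 in run 2. It is about 3 if the pre-test pools the arms, and 4 to 6 if the uncorrected version is run.
- **Adding baseline on the log scale:** 79 − 68 = 11 and 81 − 70 = 11 points.
- **Log instead of raw scale within ANCOVA:** 79 − 74 = 5 (run 2: 6.6) at s = 0.5, and 81 − 58 = 23 (run 2: 22.6) at s = 1.0.

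**The case against.** The strongest reply has four parts.

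- **The rule is fixed in advance and does not inflate false positives.** This stands. A reader might infer from a data-driven choice of test that significance is overstated or that analysts have a free hand. Neither follows: the two-step type I error is about 5%, and those analysing the results are to be blind to group (Randomization and blinding).
- **The pre-test costs little power.** This stands too. It is tempting to set 67–68% for the planned route against 79–81% for log-scale ANCOVA and blame the pre-test for the whole gap. About 11 points of that come from baseline adjustment, which is a separate matter.
- **The skewness is assumed.** Correct. It also cannot be said that the pre-test generally fails. The corrected version usually catches strong skewness, especially with arms pooled, and the 84–99% miss rates per arm at s = 0.5 to 1.0 apply only to an uncorrected test, which the article does not specify.
- **A condensed article may leave transformations and rank-based summaries to an analysis plan.** This stands in part. The lack of a named alternative to the linear model is therefore not charged as an omission. The normality rule, the comparison of means in the adjusted model and mean ± SD for the results are stated, however, and together they do not fix one effect measure.

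**Conclusion.** The point holds as a modest one. The stated method leaves the effect measure for each primary marker to a pre-test on the trial's own data, and it reports means even beside a rank-based p-value. That mismatch is visible in the Analysis section and needs no simulation.

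The size is conditional. At moderate skewness (log-SD 0.5) the choice of test is close to a coin toss. At strong skewness the corrected pre-test chooses fairly consistently, and the main loss comes from an adjusted model on the raw scale. These figures rest on lognormal data, 20 evaluable patients per arm, r = 0.5 and a 0.8 log-SD effect, none of them a trial figure except the sample size. The change is worth making for a clear estimand and, if the markers are skewed, for the power of the adjusted model; it is not needed to protect the error rate.

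**What to change.** Delete the normality pre-test as the basis for choosing a test. Before unblinding, name one primary analysis for each primary marker: ANCOVA of the final value with the baseline value as covariate, on a stated scale.

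- **TNF-α and hs-CRP, and the secondary miR-21:** natural log scale, reported as a geometric mean ratio with 95% CI.
- **TAC:** original scale, reported as a mean difference with 95% CI, unless blinded pooled data or external data point to another scale.
- **Rank-based test:** a named sensitivity analysis only.
- **Summaries:** geometric mean, or median and quartiles, for variables analysed on the log scale; mean ± SD for the others.

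The log scale is proposed because these are concentration or ratio measures; the document has no distributional data to confirm it, so record the reason for each choice.

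The cost is a change of wording, with no extra patients, visits or assays. The small downside is that effects on the log-analysed markers are read as ratios instead of differences in assay units.

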**Methods:**

This study will be a 12-week, double-blind, parallel-group, randomized, controlled trial (RCT) in which 44 patients will be allocated to ginger and placebo groups receiving basic routine treatments plus ginger or placebo capsules, respectively. The primary outcomes are inflammatory markers (TNF-α and hs-CRP) and total antioxidant capacity.

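### Percentage change from baseline is tested for every outcome: its arm means mislead for skewed markers, and the comparison has less power than baseline-adjusted ANCOVA

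*Protocol article*

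**What the plan says.** The primary outcomes are named in the abstract: "The primary outcomes are inflammatory markers (TNF-α and hs-CRP) and total antioxidant capacity". The secondary ones are clinical score and miR-21 expression. Under Hypothesis and aim, the planned comparisons are that "changes from baseline within groups and final values between groups will be evaluated"; percentage change is not mentioned there.

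The Analysis section adds it for every primary and secondary outcome: "the percentage change will be also calculated (i.e., by subtracting the beginning from the final value, dividing by the beginning value", with the result multiplied by 100. This variable "will be compared between groups by independent sample t-test or Mann-Whitney U, as well as by GLM univariate tests". For summaries, "The results will be presented as the mean ± SD"; no alternative is given for skewed variables.

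On adjustment, the same section says: "In adjusted models for confounding variables (such as the type of medication), a general linear model (GLM) (univariate type) will be used". The baseline value of the outcome is not named among the covariates, and no log transformation is mentioned. The normality check that decides between the t-test and the rank test lists age and the four laboratory variables, but not percentage change.

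**The concern.** Percentage change treats rises and falls unequally. A marker going from 10 to 20 scores +100%, and one going from 20 to 10 scores -50%. The two moves cancel, yet they average +25%. In a right-skewed marker the patients who start low can therefore dominate an arm's mean and SD. The published mean ± SD may show a rise where nothing happened, or hide a real fall.

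Dividing by baseline is also a poor way to use baseline information. With 22 patients per group planned, a comparison that wastes information costs power the trial can ill afford.

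**Working it through.** **Inputs.** From the protocol article: 22 per group and 10% loss, so 22 × 0.9 = 19.8, taken as 20 evaluable per arm; type I error 0.05, taken as two-sided because sidedness is not stated. Assumed, because the article gives neither: the SD of the log marker (s, 0.3 to 1.0) and the correlation of log baseline with log final value (r, 0.3 to 0.7). The article gives no percentage-change figure or effect size to reproduce.

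**Step 1: mean percentage change when nothing changes.** If log baseline and log final value are bivariate normal with equal means and SD s, then log(final/baseline) has mean 0 and variance 2s²(1 − r). Hence

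expected percentage change = 100 × [exp(s²(1 − r)) − 1].

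Example, s = 0.5 and r = 0.5: exp(0.125) − 1 = 13.3%. With s = 1.0 and r = 0.5: exp(0.5) − 1 = 64.9%.

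| s | r = 0.3 | r = 0.5 | r = 0.7 |
|---|---|---|---|
| 0.3 | +6.5% | +4.6% | +2.7% |
| 0.5 | +19.1% | +13.3% | +7.8% |
| 0.8 | +56.5% | +37.7% | +21.2% |
| 1.0 | +101.4% | +64.9% | +35.0% |

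For a normal marker with a CV of 10-20%, simulation gives only about 0.3-3%. At s = 0.8 and r = 0.5, an unchanged arm of 20 shows a mean rise in about 93% of simulated trials. At s = 1.0 and r = 0.5, a true 30% fall would appear as 0.70 × 1.649 − 1, about +15%.

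**Step 2: effect on the between-group test.** Under randomisation with no treatment effect, both arms share the same expected rise, so it cancels in the difference. Across the simulated grid, the type I error of the t-test on percentage change was 0.033 to 0.052.

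**Step 3: power.** Effect 0.8 log-SD, 20 per arm, r = 0.5, by simulation:

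| Analysis | s = 0.5 | s = 1.0 |
|---|---|---|
| t-test on percentage change | about 64% | about 51% |
| Mann-Whitney on percentage change | about 67% | about 67% |
| t-test on log ratio | about 70% | about 70% |
| ANCOVA on logs, baseline as covariate | about 81% | about 81% |

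The last two rows follow from theory. In units of s², the error variance is 2(1 − r) = 1.00 for the log ratio and 1 − r² = 0.75 for ANCOVA. The noncentrality is (0.8/√variance) × √(20/2): 2.53 for the log ratio (power 69%) and 2.92 for ANCOVA (power 81%).

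**Step 4: where the loss comes from.** Of the 14 points between Mann-Whitney (67%) and ANCOVA (81%), 11 (70% to 81%) come from not adjusting for baseline. About 3 come from using ranks in place of a t-test on logs. Asymmetry costs Mann-Whitney nothing, because percentage change ranks patients exactly as the log ratio does. The t-test is hurt further by skew.

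**Step 5: against the unadjusted final value.** The final value has variance 1 at every r, against 2(1 − r) for the log ratio: 1.4 at r = 0.3 and 0.6 at r = 0.7. Change is therefore worse than the final value at low correlation and better at high correlation. ANCOVA (0.91 and 0.51) beats both.

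**The case against.** The strongest reply is that percentage change is an additional analysis beside the comparison of the values themselves, that the plan allows a rank test, and that the artefact cancels between arms. Each part is right and limits the point.

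- A reader might infer that the plan will produce a false treatment effect. It will not: the expected rise is the same in both arms, and type I error is not inflated.
- A reader might take the t-test's 51% as the power of the plan. That is too harsh. Heavy skew is where the rank test would be used, and it keeps about 67%.
- A reader might conclude that percentage change is always the worse choice. It is worse than baseline adjustment in every scenario examined, but not always worse than the unadjusted test of final values (Step 5).
- A reader might expect a large rise in every outcome. The documents give no SDs, no correlations and no baseline hs-CRP values. A marker with little spread, as TAC may be, would show almost none.

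What stands: the GLM on percentage change and the mean ± SD summary have no rank alternative in the plan, so both stay exposed to skew. Even the rank test falls short of ANCOVA. The full covariate list could be in an analysis plan that is not shown, but testing percentage change for every outcome and presenting mean ± SD are choices the article itself makes.

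**Conclusion.** The point holds, in limited form. For right-skewed markers, each arm's mean ± SD of percentage change will mislead: +13% to +65% with no true change at r = 0.5 and log-SD 0.5 to 1.0, and a few percent where the CV is low. The between-group test remains valid but is less powerful than ANCOVA on logs: about 67% (Mann-Whitney) or 50-65% (t-test) against about 81%, for 20 per arm, r = 0.5 and an effect of 0.8 log-SD. Most of the shortfall of the rank test is due to the missing baseline covariate, not to the percentage scale. All sizes rest on assumed lognormal spread and correlation. The change is worth making because it is nearly free; the point does not invalidate the trial's inference.

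**What to change.** Drop percentage change as a tested variable. Make the between-group analysis of each outcome an ANCOVA of the final value on its baseline value, keeping the planned covariates such as medication type.

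- For skewed markers such as TNF-α, hs-CRP and miR-21 expression, analyse log values with log baseline. Report the back-transformed ratio of geometric means with a 95% CI, which reads directly as a percentage difference between groups.
- Analyse TAC, PMS and SCCAI on their original scale. For the clinical scores this also matches the Measurements section, which defines response in points.
- If percentage change is still wanted for readers, show it descriptively as median and IQR, without a p-value.

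Cost: a change of analysis wording and fewer tests to run; no new data. The one downside is that results for the skewed markers appear as ratios instead of raw mean percentages, which needs a sentence of explanation in the report.
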